### Sample size {14}

Based on an analysis of RCTs that have recurrent foot ulcers in people with diabetes as outcome, a risk reduction in participants with one or more recurrent foot ulcers up to 75% can be expected from a state-of-the-art multimodal treatment approach [63]. Using a more conservative estimate, we expect a risk reduction of 59% for the enhanced therapy group compared to usual care. This is based on previous studies that show that footwear and at-home foot temperature monitoring interventions combined can achieve such effect sizes [2, 15, 63]. With an expected ulcer recurrence in 37% of the participants in usual care [2, 20], this 59% risk reduction leads to a hypothesized 15% ulcer recurrence rate in the enhanced therapy group. With 15% ulcer recurrence in enhanced therapy and 37% in usual care, *α* = 0.05 (two-sided) and power = 80%, enrolment ratio of 1, power calculations show that 122 participants are required (61 per study group). We expect no dropout or missing data for the intention-to-treat analysis of the clinical outcome based on previous trial experience that clinical outcome can be obtained in each participant [20], which means that a total 122 participants are required for the primary clinical outcome.

For footwear adherence as the primary patient-related outcome measure, we expect 71% (sd 25%) adherence in usual care at 12 months based on findings from previous research [10, 12]. We expect an increase in footwear adherence in the enhanced therapy group to a level of 85% at 12 months, through the effect of indoor footwear provision [12] and structured education. With *α* = 0.05 (two-sided) and power = 80%, enrolment ratio of 1, power calculations show that 100 participants are required (50 per study group). Including a drop-out rate of 20%, this leads to a sample size of 120 participants in total for the primary patient-related outcome.

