### Statistical methods

#### Statistical methods for primary and secondary outcomes {20a}

Statistical analysis will be performed after the last follow-up visit of the last participant using SPSS statistical software (IBM Corporation, Armonk, NY). All tests will assess group effects, will be two-sided, and use *P* < 0.05 as significance level. All comparisons between groups are based on both intention-to-treat and final visit end-point analysis.

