#### Methods for additional analyses (e.g., subgroup analyses) {20b}

Various per-protocol analyses will be done, consisting of (i) adherence to the modalities in enhanced therapy and (ii) adherence to each specific modality in enhanced therapy, comparing adherent participants with both non-adherent participants and with the control group, and (iii) for each modality that is part of the intervention, we will compare outcomes of all participants who received that modality (including those in usual care, since the separate parts of the intervention can be provided in usual care) with participants who did not receive that modality.

Subgroup analyses will be done based on gender, ethnicity, disease severity (e.g., ulcer history, comorbidities), education level, and disease perceptions (e.g., perceived ulcer risk), to assess their associations with all outcomes.

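### The stated aim of the subgroup analyses is prognostic: they relate characteristics to outcomes and do not ask whether the effect of enhanced therapy differs between subgroups

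*Protocol article*

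**What the plan says.** One sentence in the protocol article, under Methods for additional analyses {20b}, covers subgroups. It begins "Subgroup analyses will be done based on gender, ethnicity, disease severity (e.g., ulcer history, comorbidities), education level" and ends "disease perceptions (e.g., perceived ulcer risk), to assess their associations with all outcomes". It names no test or model. The article nowhere mentions an interaction term, effect modification or a treatment effect by subgroup.

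The general rule, under Statistical methods for primary and secondary outcomes {20a}, is "All tests will assess group effects, will be two-sided, and use" a 0.05 significance level.

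**The concern.** In a randomized trial, a subgroup analysis normally asks whether the treatment effect varies with a characteristic. The possessive in the quoted sentence refers to the characteristics, so the stated target is the relation of characteristic to outcome. That is a different question. Its null hypothesis is false for any real risk factor, even if enhanced therapy helps everyone equally. Conversely, it can be true when the benefit differs.

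At stake is interpretation. The intervention is built on personalization, so readers will want to know who gains from it. Five families of characteristics related to all outcomes at the 0.05 level will probably produce several significant results under the label of subgroup analysis. None of them would say anything about who gains.

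**Working it through.** **Inputs from Sample size {14}.** Ulcer recurrence: "With 15% ulcer recurrence in enhanced therapy and 37% in usual care", with alpha "0.05 (two-sided) and power = 80%, enrolment ratio of 1". Adherence: "we expect 71% (sd 25%) adherence in usual care at 12 months" against 85% in enhanced therapy, a 14-point difference. Planned total 126; about 100 analysed for adherence after 20% drop-out.

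**Assumptions, not in the article.** A two-level characteristic, split 50/50 unless stated, and the subgroup patterns given below.

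**1. The plan's own figure.** With a mean risk of 0.26, n per arm = [1.96·√(2·0.26·0.74) + 0.842·√(0.37·0.63 + 0.15·0.85)]² / 0.22² = 61.2. The article states 61 per arm (122 in total), so the figure reproduces. Power is 79.9% at 61 per arm and 81.1% at 63. No figure is given for any subgroup analysis.

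**2. Characteristic against outcome, with the same treatment effect in both subgroups.**
- Adherence: the SD over both arms is √(25² + 7²) = 25.96, because each arm mean lies 7 points from the overall mean. With 63 per subgroup, SE = 25.96·√(2/63) = 4.63.
  - Prognostic gap of 10 points: z = 2.16, power Φ(2.16 − 1.96) = 58%.
  - Gap of 12.5 points: z = 2.70, power 77%.
  - Simulation (4,000 trials each) gave 58.1% and 76.8%; the interaction test rejected in 4.8% and 5.4%.
  - With 100 analysed, SE = 25.96·√(2/50) = 5.19, and the two figures fall to 49% and 67%.
- Ulcers, same risk difference of 0.22 in both subgroups (usual care 26% and 48%, enhanced therapy 4% and 26%): the subgroup averages are 15% and 37%. Simulation (20,000 trials) gave 81% for association and 6% for interaction.
- Ulcers, same relative risk of 15/37 = 0.405 (usual care 25% and 49%): the subgroup averages are 17.6% and 34.4%, and the association test rejects in 59%.

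**3. Arm comparisons within each subgroup, with the same 14-point adherence effect in both.** With 31.5 per arm in each subgroup, SE = 25·√(2/31.5) = 6.30, z = 14/6.30 = 2.22, power 60%. The chance that exactly one of the two subgroups is significant is 2·0.60·0.40 = 48%. With 100 analysed, SE is 7.07, power 51%, and the chance 50%. About half of such trials would appear to show benefit in one subgroup only, although the effect is identical.

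**4. Power of an interaction as large as the planned overall effect.**
- Adherence, 14 points: SE = 25·√(4/31.5) = 8.91 at 126 and 10.0 at 100. Power is 35% and 29%; with a 70/30 split, 30% and 25%. The 95% half-width is 1.96·8.91 = 17.5 points or 1.96·10 = 19.6 points.
- Ulcers, 0.22 on the risk-difference scale, N = 126, usual care 37%, effects either 0.33 against 0.11 or 0.22 against 0: SE is 0.149 or 0.162 and power 32% or 27%. It is 25% or 23% with a 70/30 split, and 20% or 18% with 80/20. The 50/50 half-width is 0.29 to 0.32.
- For 80% power on ulcers, about 454 to 538 participants would be needed (50/50), or 586 to 672 (70/30).

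**The case against.** The strongest defence is that the sentence is loose wording. It sits under a subgroup heading, names no test, and follows a general rule that tests assess group effects, so it may mean comparing the arms across these subgroups. The article condenses a fuller protocol, and model details may be given there. The listed objectives do not promise to find out who benefits, and exploring prognosis is legitimate.

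Part of this stands. The article does not commit to a pooled test that ignores treatment arm, and it does not say that associations will be presented as differences in benefit. A reader might infer either, but the text supports neither.

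The rest does not remove the point. The article does fix a target, and the target is prognostic. Under Other study outcomes it uses association in the same prognostic sense, to select stratification variables, and it names the two arms when it means a treatment comparison. The charitable reading leads only to step 3 of the working, which is not a test of a difference in effect.

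A reader might also infer that the planned analysis misses real differences in benefit that an interaction test would catch. An extreme case suggests so: an adherence effect of 28 points in one subgroup and 0 in the other, with equal subgroup averages, is found by the association test in 4% of trials and by the interaction test in 88%. That requires an interaction twice the planned effect, a prognostic difference that exactly cancels it, and no drop-out; with 100 analysed, 28/10 = 2.8 gives about 80%. In a more moderate case (usual care 37% in both subgroups, enhanced therapy 26% and 4%), association rejects in 30% and interaction in 33%. Better detection is therefore not the argument.

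**Conclusion.** The point holds as a matter of target and interpretation. As written, the subgroup analyses address prognosis. In the examples, a characteristic with no bearing on the treatment effect is significant in about 58% to 81% of trials at N = 126 (49% to 67% for adherence with 100 analysed). These percentages depend on the assumed prognostic gaps and the equal split; the direction of the problem does not. Neither the literal nor the charitable reading tests whether the effect differs between subgroups.

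The consequence is limited. The sample size and the analyses of the three primary outcomes are untouched. Correcting the target would not make subgroup differences reliably detectable, since power is roughly 18% to 35% for an effect-sized interaction. This is a minor improvement to a secondary analysis.

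**What to change.** Replace the stated aim with the following. For each primary outcome, report the enhanced-minus-usual-care difference within each subgroup and the treatment-by-characteristic interaction with a 95% confidence interval, labelled exploratory. For ulcer recurrence, name the scale, for example the risk difference, because an effect that is constant on one scale need not be constant on another. Define subgroups by baseline values only. This matters most for disease perceptions if they come from the study questionnaire, which is repeated at 6 and 12 months, when the education may already have changed the answers. If associations with outcomes are also wanted, report them separately under the name of prognostic analyses.

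The cost is one reworded sentence and one interaction term per model, with no new data or participants. The downside is wide intervals (about ±17 to ±20 adherence points, or about ±0.3 in ulcer risk, with equal subgroups), so the text should say that a non-significant interaction is not evidence of a uniform effect.

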#### Methods in analysis to handle protocol non-adherence and any statistical methods to handle missing data {20c}

As the first choice, missing data will be imputed using multiple imputation with a fully conditional specific predictive mean matching model. Baseline characteristics that significantly differ between those with complete and those with missing data will be used as predictors. For sensitivity analysis, other imputation strategies (e.g., with fewer predictors, or single imputation strategies using individual or group means) will be applied as well.

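### The stated predictor rule for multiple imputation does not admit randomised arm; applied as written, it shrinks the adherence difference by about the missing fraction

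*Protocol article*

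**What the plan says.** The protocol article, section {20c}, states that "missing data will be imputed using multiple imputation with a fully conditional specific predictive mean matching model" as the first choice. It then gives its one predictor rule: "Baseline characteristics that significantly differ between those with complete and those with missing data will be used as predictors". It names neither arm, nor the randomisation strata, nor follow-up values of the outcome. The sensitivity analyses offered as examples are imputation "with fewer predictors, or single imputation strategies using individual or group means".

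Section {20a} analyses adherence by an unadjusted independent-samples t-test and bootstraps cost-utility within study group. Section {12} measures adherence at baseline, 6 and 12 months, and EQ-5D-5L every 3 months. For adherence, section {14} plans on these inputs: "we expect 71% (sd 25%) adherence in usual care at 12 months", a rise "to a level of 85% at 12 months" with enhanced therapy, and, for attrition, "Including a drop-out rate of 20" per cent.

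**The concern.** An imputation model should contain every variable on which the later analysis conditions. The t-test compares arms, but the stated rule gives arm no way in. Arm is not a baseline characteristic. It is also fully observed, so a fully conditional specification does not bring it in as one of the incomplete variables; it has to be named. Without it, imputed participants in both groups are given values from the same distribution and add almost no treatment contrast, while still counting towards the sample size.

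The screen is a second weakness. It keeps variables that differ by missingness and ignores how well they predict the outcome. With about 25 incomplete cases among 126 participants, it would also drop many useful predictors by chance.

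At stake are the estimate and power for adherence, one of three primary outcomes, and the QALY component of another.

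**Working it through.** **Inputs from the protocol article.** Adherence 71% versus 85% (difference 14 points), SD 25, two-sided 0.05, power 80%, 20% drop-out, from {14}. QALY difference 0.10, SD 0.15, from {14}. Total 126, so 63 per arm. **Assumed, not in the documents:** correlation 0.5 between baseline and final outcome; values missing completely at random; missing fractions of 10% and 30% to bracket the planned 20%.

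**1. The plan's own figure.** n per arm = 2 × (1.96 + 0.8416)² × (25/14)² ≈ 50.1. That rounds up to 51, against the stated 50. At 50 per arm the power is 0.7996 by the normal formula, so the planned figure is reproduced.

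**2. Shrinkage by hand.** Without arm, and with baseline covariates balanced by randomisation, an imputed value has the same expectation in both arms, namely the pooled mean (71 + 85)/2 = 78. With missing fraction m, each arm's completed mean is (1 − m) × its own mean + m × 78. At m = 0.20:
- enhanced therapy: 0.8 × 85 + 0.2 × 78 = 83.6
- usual care: 0.8 × 71 + 0.2 × 78 = 72.4
- difference: 11.2 = 14 × 0.8

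Likewise 14 × 0.9 = 12.6 and 14 × 0.7 = 9.8.

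**3. Simulation with the named method.** Predictive mean matching (5 donors, 10 imputations, 600 replicates), Rubin's rules and a t-type test, at 63 per arm. In each cell the first figure is for a model with an unrelated covariate and the second for a model with the baseline outcome. Simulation error is about 0.2 points for the adherence estimates and about 0.02 for power.

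| Outcome | Missing | Arm omitted: estimate | Power | Arm included: estimate | Power |
|---|---|---|---|---|---|
| Adherence | 10% | 12.7 / 12.6 | 0.78 / 0.78 | 13.6 / 13.8 | 0.83 / 0.84 |
| Adherence | 20% | 11.1 / 11.3 | 0.64 / 0.64 | 14.0 / 14.0 | 0.75 / 0.80 |
| Adherence | 30% | 9.9 / 9.7 | 0.48 / 0.47 | 13.7 / 13.7 | 0.67 / 0.74 |
| QALY | 20% | 0.079 / 0.079 | 0.81 / 0.81 | 0.100 / 0.099 | 0.88 / 0.91 |

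Adding the baseline outcome without arm does not remove the shrinkage (11.3). Adding arm without the baseline outcome does (14.0). So the shrinkage comes from omitting arm; leaving out the baseline outcome costs precision only (0.75 against 0.80).

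Dropping incomplete cases at 20% missing leaves 63 × 0.8 = 50.4 per arm, which by step 1 has power of about 0.80. Under these assumptions, imputing without arm is therefore worse than not imputing at all.

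**4. What the screen can detect.** At 20% missing, about 25 of 126 participants are compared with 101. For 80% power a baseline variable must differ by 2.8 × √(1/101 + 1/25) ≈ 0.63 SD. Smaller differences would often be screened out, however well the variable predicts the outcome.

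**5. Mean imputation within arm.** Filling 20% of values with the arm mean leaves the difference at 14, but cuts the variance to about 0.8 × 625 while counting 63 per arm. The nominal standard error is √(2 × 0.8 × 625/63) ≈ 3.98, against √(2 × 625/50.4) ≈ 4.98 from the data actually observed. Intervals are about 20% too narrow.

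**The case against.** The strongest reply is that the text never restricts predictors to the screened baseline variables and never rules out arm. A journal article commonly leaves the full predictor list to a later document. This stands as a limit on the claim: a reader might infer that the protocol deliberately excludes arm, and the documents do not support that. It does not dispose of the point, because the article goes beyond silence. It fixes a selection rule, and arm fails it.

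A reader might also infer that the same person's earlier outcome values go unused. That is not supported either. Baseline adherence and EQ-5D-5L could pass as baseline characteristics, and a fully conditional model can carry the interim visits as mutual predictors. If 6-month adherence enters with pooled slope b, is observed in those who later drop out and shows the same 14-point effect, the expected difference is 14 × (1 − m(1 − b)). At m = 0.20 that is 11.2 for b = 0, 12.6 for b = 0.5 and 14 only for b = 1. Interim values would soften the shrinkage but would not reliably remove it.

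On the sensitivity analyses, section {20a} uses the word group for study arm. Taken that way, "single imputation strategies using individual or group means" may preserve the contrast and so partly check the bias. That is plausible, though {20c} does not define the term. The resulting intervals would still be too narrow, and using fewer predictors cannot bring arm in.

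Finally, the clinical outcome is largely untouched: {14} expects no missing ulcer data, and {18b} has its own rule for withdrawals and deaths.

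**Conclusion.** The predictor rule is poorly chosen and should be replaced. Applied as written, without arm, it shrinks the adherence difference by about the missing fraction. At the plan's own 20% that is 14 to about 11.2 points, with power of about 0.64 instead of 0.80. The range over 10% to 30% missing is 12.6 to 9.8 points and power of about 0.78 to 0.47. These figures assume 63 per arm, a baseline correlation of 0.5, data missing completely at random and no post-randomisation outcome values in the model.

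For QALYs the difference falls from 0.10 to about 0.08 at 20% missing if whole QALYs are imputed, and by less if only some EQ-5D-5L visits are missing. It would be tempting to say that power for the health-economic outcome is lost as well. The calculation does not show this: power for a test on QALYs alone stays at about 0.81 at 20% missing, and that is not a test of net monetary benefit.

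**What to change.** Replace the predictor sentence in {20c}. State that imputation is done separately by arm, or with coded arm in the model. Include the randomisation strata and the baseline and interim values of the outcome being imputed (adherence at 0 and 6 months; EQ-5D-5L and costs by visit). Keep variables related to missingness as additional predictors, with no significance screen. State that single mean imputation will not be relied on for inference.

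The cost is one paragraph of analysis wording, written before the analysis that {20a} places after the last participant's final visit. All the variables are already collected, and a coded arm keeps the blinded analyst of {17a} blinded.

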##### Primary study outcomes

For each of the three specified outcomes related to proportion of participants with a recurrent foot ulcer (any ulcer, plantar ulcer, ulcer at high-risk location), effectiveness of the intervention will be assessed using chi-square analysis. Outcome of ulcer recurrence over time will be assessed using log-rank testing and presented as Kaplan–Meier plots censored for death. For adherence to wearing custom-made footwear, Student’s *T*-test for independent samples will be done, provided the data is normally distributed. Cost and utility outcomes will be combined in the economic evaluation to calculate cost (savings) per QALY (gained) per participant (i.e., cost-utility). Incremental cost-utility ratios (ICUR) will be calculated as the ratio between costs and QALY differences between enhanced therapy and usual care. To account for sampling variability, non-parametric bootstrapping stratified for group and participating center category will be done with 5000 replications. Results will be displayed graphically by plotting the bootstrapped differences in costs and QALYs in a cost-utility plane, with the percentage of pairs in each quadrant calculated. Finally, cost-utility acceptability curves (CUAC) for willingness to pay values up to €100,000 will be graphically displayed, with the probability of enhanced therapy being cost-effective over usual care calculated for willingness-to-pay levels of €0,- and €50,000 per QALY gained and €0,- and €20,000 per extra participant without foot ulcer recurrence, respectively.

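### Mean imputation is named as a missing-data sensitivity analysis: study-arm means would give about 12% false positives for adherence at 20% drop-out, other readings dilute a real effect, and no named option departs from missing at random in a controlled way

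*Protocol article*

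**What the plan says.** The missing-data section {20c} of the protocol article sets the main method: "As the first choice, missing data will be imputed using multiple imputation with a fully conditional specific predictive mean matching model". Its predictors are the baseline characteristics that differ significantly between participants with complete and with missing data. For sensitivity analysis, "other imputation strategies (e.g., with fewer predictors, or single imputation strategies using individual or group means) will be applied as well". The section does not say whether a group is a study arm or the whole sample, or which of a participant's measurements form an individual mean.

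The Sample size section {14} plans for loss on adherence: "Including a drop-out rate of 20%, this leads to a sample size of 120 participants in total". The same 20% is allowed for cost-utility, where the total is 63 per arm. No missing data are expected for the ulcer outcome, and the retention section {18b} gives that outcome its own rule for withdrawal without consent to use of medical files and for death.

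On testing, section {20a} states: "All tests will assess group effects, will be two-sided, and use" a 0.05 level. The test for adherence is a two-sample t-test ("For adherence to wearing custom-made footwear, Student’s" test for independent samples, if the data are normally distributed). Adherence is measured at baseline, 6 months and 12 months (Outcomes {12}).

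**The concern.** A sensitivity analysis for missing data should show whether the conclusion survives a different, credible assumption about the values that were not seen. Filling gaps with a mean does not do that.

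A single filled value is treated as if it had been observed. With the study-arm mean, the filled values add no spread but are counted in the sample size, so the standard error is too small. With the pooled mean, both arms are pulled toward each other. With the participant's own mean, values from before the intervention took effect can enter a 12-month outcome. Using fewer predictors in the multiple imputation gives a thinner model of the same missing-at-random type.

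These checks will be used to judge two of the three primary outcomes, each planned with 20% loss. A check that overstates precision can seem to confirm a result it has not tested. Leavers may also differ from stayers: the Background describes daily self-management as a burden to which thermometry adds, and study thermometry is part of the enhanced arm only. That makes informative drop-out plausible, not established.

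**Working it through.** **Inputs from the protocol.** Usual care: "we expect 71% (sd 25%) adherence in usual care at 12 months based on findings from previous research". Enhanced therapy: "We expect an increase in footwear adherence in the enhanced therapy group to a level of 85% at 12 months". The difference is therefore 14 points and the SD 25. The t-test is two-sided at 0.05, with 20% drop-out and 63 per arm. I take n = 63 randomised and m = 50 observed per arm (63 × 0.8 = 50.4).

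**The plan's own figure.** n per arm = 2 × 25² × (1.96 + 0.8416)² / 14² = 50.06. The plan's 50 per arm gives power 0.7996, so its 100 is reproduced to within rounding (rounding up gives 51 per arm). Its 120 is 100 × 1.2. The protocol states no error rate for the imputation strategies, so there is none to reproduce.

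**Study-arm mean.**
- The filled arm keeps the observed mean, so the true standard error of the difference is that of the complete cases: 25 × √(2/50) = 5.0.
- The t-test divides the same sum of squares by n − 1 instead of m − 1, and then by n instead of m. The ratio of nominal to true standard error is r = √[m(m − 1) / (n(n − 1))] = √[(50 × 49) / (63 × 62)] = 0.792, about 20% too small.
- Type I error = 2 × [1 − Φ(1.96 × 0.792)] = 12.1%. Coverage is 1 minus this, about 88%.
- Apparent power = Φ(14/5 − 1.96 × 0.792) = Φ(1.248) = 89%. Complete cases give Φ(2.8 − 1.96) = 80%.
- With 60 per arm and 48 observed, type I error is 11.8%. With 63 per arm it is 6.2%, 7.6% and 17.3% at 5%, 10% and 30% missing.

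**Pooled mean.**
- The filled values are the same in both arms, so the expected difference is 14 × 50/63 = 11.1 points.
- The standard error shrinks with it. Under no effect, simulated type I error is 4.8 to 5.2%. With a true 14-point effect, coverage is about 89%, and rejection is as frequent as with complete cases (79.6% each in one simulation, 79.2% each in another).

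**Individual mean.**
- Simulated type I error with the mean of the two other visits is 4.9 to 5.2%, for between-visit correlations of 0.3 to 0.9. These correlations are assumed, as the protocol gives none.
- For the effect, assume both arms start at 71 and the enhanced arm reaches 85 by 6 months. A missing 12-month value is then filled with (71 + 85)/2 = 78 in the enhanced arm and 71 in usual care, a difference of 7. The overall difference becomes 14 × 50/63 + 7 × 13/63 = 11.1 + 1.4 = 12.5 points.

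**Simulation check.** In 20,000 trials per setting, with normal data missing completely at random, arm-mean filling gave 11.9 to 12.4% type I error. Complete cases gave 4.8 to 5.2%.

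| Method, 20% missing | Type I error | Estimate of a 14-point effect | 95% coverage at that effect |
|---|---|---|---|
| Complete cases | about 5% | 14 | about 95% |
| Study-arm mean | about 12% | 14 | about 88% |
| Pooled mean | about 5% | about 11 | about 89% |
| Individual mean (baseline and 6 months) | about 5% | about 12.5 | not relied on here |

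**The case against.** Multiple imputation governs the main result, the mean imputations are additional, and nothing lets a sensitivity result replace the primary one. That stands, and it limits the weight of the point. Several stronger readings are tempting but not supported:

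- **That 12% is the trial's false-positive rate.** It is not. It belongs to one reading of one sensitivity analysis.
- **That every mean-based option gives 12%.** Individual and pooled means keep about 5% under no effect. Only the study-arm reading inflates the error, and the text does not say that this reading is meant.
- **That pooled-mean filling would overturn a true positive finding.** It biases the estimate toward zero, but it rejects as often as complete cases do.
- **That all named options are weaker versions of the first-choice model.** An individual mean uses the participant's own other visits and assumes that the person's level is stable. This is a different assumption, though not a controlled departure from missing at random.
- **That the trial has no missing-not-at-random analysis.** The list is introduced as examples, and neither the full protocol nor an analysis plan is at hand. Only the named examples can be judged.
- **That the 12% carries over to cost-utility.** That analysis is bootstrapped, and a participant who leaves may have contributed some of the three-monthly costs and utilities. No figure was computed for it.

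The argument for informative drop-out also has limits. Section {11a} allows thermometry to be adapted or stopped without leaving the trial, and section {6b} says usual care may include some of the same interventions.

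What the objection does not remove is that the article commits to these methods by name. This is a stated choice, not a detail left out.

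**Conclusion.** The point holds as a fault in the named sensitivity analyses. On the study-arm reading, the adherence t-test has a standard error about 20% too small, type I error of about 12%, coverage of about 88%, and apparent power of about 89% against about 80%. On the pooled reading, a 14-point effect is reported as about 11 points with about 89% coverage. Individual means are sound under no effect but dilute a real one to about 12.5 points if baseline enters the mean. None of the named options varies the missing-at-random assumption in a controlled way.

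The figures rest on the plan's SD of 25, 63 per arm, 50 observed in each, normal data and values missing completely at random. The 12.5 also assumes that the full effect is present by 6 months. The point applies to sensitivity analyses of adherence and, without a figure, of cost-utility. The primary multiple imputation and the ulcer outcome are not affected. It should be changed, but it does not threaten the trial's main analysis.

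**What to change.** In section {20c}, delete single imputation by individual or group means. Name instead a delta-adjusted multiple imputation for 12-month adherence, QALYs and costs:

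- start from the first-choice imputation model;
- shift the imputed values in each arm separately, over a range fixed before the data are analysed;
- for adherence, pool the estimates with Rubin's rules at each shift; for cost-utility, state how the imputed sets are combined with the planned bootstrap;
- report the shift, or pair of shifts, at which the conclusion changes.

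The range for each outcome is for the sponsor to choose and justify. If the full protocol or analysis plan already contains such an analysis, it is enough to refer to it and remove the mean imputations.

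The cost is a change of wording and a little extra programming. No new data, visits or participants are needed.
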